### Ethics approval

Isfahan University of Medical Sciences' ethics committee has approved and accepted the whole protocol (IR.MUI.MED.REC.1402.466). A registration number is available in the Iranian Registry of Clinical Trials (IRCT20201129049534N8). Prior to participating in the study, patients or their legal guardians must fill out the written informed consent form. Throughout the collection process, laboratory specimens, and reports, each patient will be assigned a unique ID number. Research teams will only be able to access the collected data during research and these will remain strictly confidential. Dataset access rights will also be granted to the corresponding author.

### Safety consideration

Several studies have shown that saffron consumption up to 1.5 grams per day is safe in humans (Mehri et al. 2020; Zeinali et al. 2019). Some studies have reported no side effects of saffron, but a small number have reported minor side effects such as dizziness, dry mouth, headache, fatigue, nausea, constipation, and sweating (Zeinali et al. 2019). Hence, at the doses mentioned, saffron and placebo will not cause substantial adverse effects. Nevertheless, minor side effects will be reported to the Isfahan University of Medical Sciences Ethics Committee for consideration.

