### Exclusion criteria

Dissatisfaction of the patient or his legal guardian. Patients who stay in the ICU for <48hr. Patients receiving parenteral nutrition. Patients receiving enteral or oral nutrition initially but transferring to parenteral nutrition due to contraindications. Patients who are incapable of receiving enteral nutrition or who may not be able to receive enteral nutrition in the future as a result of incomplete resuscitation and hemodynamic instability or gastrointestinal disorders such as nausea, persistent vomiting, ileus, obstruction of the intestinal tract, diarrhea that exceeds 500 ml per day, and high-output fistulas. Cancer patients undergoing chemotherapy. Patients suffering from pancreatitis, kidney failure, or congenital or immune disorders. Patients taking phenobarbital, levetiracetam, or phenytoin. Dialysis patients, patients with severe septic shock or sepsis, or DIC (diffuse intravascular coagulation). Pregnancy and breastfeeding. Patients with BMI < 18.5 kg/m^2^. Patients who need blood transfusions frequently. Unwanted side effects associated with taking supplements or placebos. ICU patients who are expected to die within 2 days of admission. Patients who take other herbal supplements. Patients with a spice or herbal supplement allergy. Patients with GCS levels less than 3 or greater than 13. Patients who passed away during the trial

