Another factor contributing to sepsis pathogenesis is the inflammatory reactions (Arina and Singer 2021). During an inflammatory reaction, neutrophils and macrophages release cytokines like TNF-alpha, interleukins and prostaglandins. Inhibiting fibrinolysis is one of the functions of cytokines. They activate the extrinsic coagulation cascade (Theofilis et al. 2021). Microvascular thrombosis results from these overlapping processes and organ dysfunction can be caused by thrombosis (Bray et al. 2020). Saffron can reduce inflammatory factors and affect coagulation cascades through various pathways. 

In a randomized, double-blind, placebo-controlled clinical trial, saffron consumption significantly reduced inflammation, especially levels of IL-6 and TNF-a in diabetics (Mobasseri et al. 2020). The consumption of saffron also reduced some blood parameters, including red blood cells, hemoglobin, hematocrit, and platelets (Mehri et al. 2020). Another study assessed 70 ICU patients with sepsis. In this study patients were divided into a control group, which received continuous blood purification treatment, and a treatment group that received continuous blood purification along with SESYA treatment, an extract of saffron known as saffron yellow A. The results revealed that, compared to the control group, the treatment group experienced a significant reduction in serum functional indicators including lactic acid, procalcitonin, CRP, and coagulation function indicators. Additionally, the treatment group demonstrated improved quality of life scores. Both groups showed a substantial decrease in organ function indicators after treatment, with the treatment group exhibiting significantly greater improvement than the control group (Wang et al. 2023). In addition, saffron was shown to improve levels of ESR, CRP, TNF-alpha, MDA, and TAC in patients with rheumatoid arthritis when given at a daily dosage of 100 mg (Hamidi et al. 2020). A meta-analysis study showed that supplementing with saffron can significantly reduce CRP levels in people with CRP levels above 3 (Asbaghi et al. 2021). 

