Saffron's medicinal properties can be attributed to volatile and nonvolatile compounds. Safranal, crocin, kaempferol, picrocrocin, crocetin, and a variety of carotenes are among the most important bioactive compounds found in Crocus sativus stigmas (Husaini et al. 2021). Therefore, saffron supplementation appears to be effective in treating sepsis due to its antioxidant, anti-inflammatory, and anticoagulant properties. However, there is still lack of information regarding saffron's potential to improve clinical outcomes in sepsis patients and the underlying mechanisms. To address this critical research gap, this trial will examine how saffron supplementation affects oxidative stress biomarkers, inflammation factors, and clinical outcomes in patients admitted to ICU with sepsis.  

To increase the safety of the intervention, a dose of 100 mg saffron per day will be used, which is completely safe, and previous studies have shown that the use of saffron up to 1.5 grams per day is safe in humans (Mehri et al. 2020).

It should be acknowledged that while this study will be the first randomized double-blind clinical trial to investigate saffron's effects on sepsis, there are some limitations, including the short intervention duration and the lack of long-term follow-up. Additionally, saffron cannot be used as a monotherapy for ethical reasons.

Lastly, if this supplement proves effective in managing sepsis, it could represent a very attractive adjunctive therapy and could have an impact on future medical policy regarding saffron use as an auxiliary treatment for sepsis patients.

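### The stated safety reporting names only minor side effects, and the exclusion list removes patients with side effects or who die, so a safety comparison built on these rules would understate harm

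*Protocol article*

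**What the plan says.** **Safety consideration.** After citing earlier studies, the section concludes: "Hence, at the doses mentioned, saffron and placebo will not cause substantial adverse effects". The reporting commitment that follows is that "minor side effects will be reported to the Isfahan University of Medical Sciences Ethics Committee for consideration". No other safety reporting is stated there.

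**Discussion.** The dose is justified in the words "a dose of 100 mg saffron per day will be used, which is completely safe". The same Discussion states: "The consumption of saffron also reduced some blood parameters, including red blood cells, hemoglobin, hematocrit, and platelets". It also expects benefit in sepsis "due to its antioxidant, anti-inflammatory, and anticoagulant properties".

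**Exclusion criteria.** The list includes "Unwanted side effects associated with taking supplements or placebos" and, as its last item, patients who die during the trial.

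**Outcome assessment, Laboratory assessment and Table 1.** CBC and 28-day mortality are secondary outcomes. Blood is drawn at the beginning and end, which Table 1 places at days 1 and 7. Table 1 also has an adverse-events row with no restriction to minor events. Its cells are blank in the text available, as are those of the two treatment rows above it, so nothing is inferred from the blanks.

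**Statistical methods.** An intention-to-treat analysis is named as the approach to missing data.

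**The concern.** Two stated rules act in the same direction. The reporting rule is written around the premise that nothing substantial will happen, so serious and bleeding events are not named in the one commitment the article makes. The exclusion list then names the patients in whom harm would show: those with side effects and those who die.

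The premise also sits badly with the Discussion, which describes falls in red-cell measures and platelets and an anticoagulant action. The Introduction says that sepsis itself brings problems of coagulation factors and platelets. At stake is whether the eventual report can support a statement about safety. If affected patients are left out, a reassuring table would partly reflect who was counted.

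**Working it through.** The plan gives no safety figure to reproduce, so the check sets the sections side by side and then works out the direction of the error.

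**1. Premise against Discussion.** The Safety consideration section expects no substantial effect, and the Discussion calls the dose completely safe. The Discussion also reports lower haemoglobin and platelets and names an anticoagulant property. It gives no dose, population or size for the blood-count effect, and it cites the same source for that effect as for safety up to 1.5 g per day. So the statements need reconciling, but the article does not show the effect at 100 mg for 7 days.

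**2. Timing of the two exclusions.** A side effect of the supplement or placebo can occur only once a tablet has been given, and death during the trial only once the patient is in it. Neither can be screened for at entry, so in effect both remove patients after randomisation.

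**3. Exclusions against outcomes and analysis set.**
- 28-day mortality is a secondary outcome, yet patients who die during the trial are listed for exclusion. The Intervention section uses the word trial for the 7 days of treatment. On that reading deaths in the first 7 days are removed; if the word covers follow-up, all deaths to day 28 are.
- Intention-to-treat keeps patients as randomised, whereas the exclusion list takes some out. The article does not say which prevails.

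**4. Direction of the error.** Let an arm have n randomised patients, of whom e have an event, and let r of those e be removed.
- Risk with everyone counted: e / n.
- Risk after removal: (e − r) / (n − r).
- (e − r) / (n − r) < e / n is equivalent to n(e − r) < e(n − r), that is, to rn > re. This holds whenever r > 0 and e < n.

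So the risk in each arm is understated whenever any affected patient is removed.

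**5. Effect on the comparison.** Suppose the same fraction f of affected patients is removed in both arms. A true risk p becomes p(1 − f) / (1 − pf), with slope (1 − f) / (1 − pf)² in p. For p below one half, (1 − pf)² > (1 − f/2)² ≥ 1 − f, so the slope is below 1 and the risk difference shrinks towards zero. If the arms lose different fractions, the direction of the error in the difference is not guaranteed.

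**6. Room for removal.** The sample-size section needs 35 per group and enrols 45 to cover attrition: 45 − 35 = 10 per arm, and 10 / 45 = 22%. The article does not divide this between side effects, deaths and other reasons. Within the planned allowance, the share of an arm removed for side effects or death could lie anywhere from 0 to 22%.

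**The case against.** The strongest reply is that the word *minor* can be read as *even minor*: after a sentence expecting nothing substantial, the authors may mean that they will report small effects too. Nothing in the article says that serious events go unrecorded. The adverse-events row in Table 1 is unqualified. Haemoglobin and platelets come with the planned CBC, which falls under the between-group tests, and mortality is followed by phone. Bleeding risk is partly handled at entry, because patients with DIC and those who often need transfusion are excluded. Intention-to-treat is stated, and a withdrawal for side effects can itself be counted as an event. Finally, definitions and routes for serious events are commonly left to the full protocol.

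Much of this stands. A reader might infer that serious harm will not be collected, or that the observed event rate is bound to be zero. The article supports neither, for the reasons just given. Nor can one infer that saffron at the trial dose causes bleeding or low counts, since the Discussion gives no dose for that effect. An upper limit for zero events among 45 patients does not measure the problem either, because it applies to any arm of that size even with perfect reporting.

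What the reply does not remove is the text itself. The article states a reporting rule whose wording stops at minor effects, and an exclusion list that contradicts its own mortality outcome and analysis principle. These are stated rules, not detail left for elsewhere.

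**Conclusion.** The point holds as a limited one. The stated reporting commitment is too narrow for the article's own account of saffron. The exclusions for side effects and death conflict with the 28-day mortality outcome and with intention-to-treat. Harm would not be wholly unseen, but a safety comparison that leaves out affected patients would understate the risk in each arm. For risks below one half and equal removal, it would also pull the arms together.

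The size cannot be fixed from the article. It depends on how many patients are removed for these reasons, for which the only guide is the attrition allowance of 10 of 45 per arm. The conclusion assumes that the exclusion list is applied as written. If intention-to-treat prevails and all events are tabulated, no bias arises and only the wording needs correcting.

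**What to change.** - **Safety consideration:** replace the reference to minor side effects with all adverse events, including serious and bleeding events, tabulated by arm for every randomised patient.
- **Exclusion criteria, Outcome assessment and Statistical methods:** reconcile the three. State that patients who stop for side effects or who die stay in the safety and mortality analyses.
- **CBC:** state that the planned comparison of haemoglobin and platelets uses all randomised patients with available data.
- **Safety statements:** reconcile those in Safety consideration and the Discussion with the blood-count and anticoagulant statements in the same Discussion.

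The cost is slightly more event recording and one extra table. No new blood draw is needed, and the sample size does not change.

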### Power calculation and sample size estimates

Using the formula for randomized clinical trials, the sample size was calculated considering type I error at 5% and type II error at 20% (β = 0.2; power = 80%). CRP level was considered a main outcome, and based on a previous study, the sample size was calculated to be 35 persons for each group (Δ = 3) (Rai et al. 2017). Considering attrition, 90 patients will be considered in total, 45 in each group.

### Outcome assessment

Our primary outcomes will be serum levels of CRP, TNF-α, IL-6, IL-18, and ESR as a marker of inflammation, serum LDH as an indicator of cell damage, TAC, SOD, GPx, MDA and catalase as an indicator of oxidative stress that will be measured at the beginning and end of the study. In addition, the 28-day mortality rate, GCS, CBC, APACHE II Score, SOFA score, and NUTRIC score are secondary outcomes. Anthropometric variables including weight, height, body mass index (BMI), and calf circumference will be assessed at baseline of the study (Table 1). Mid arm circumference (MAC) will be assessed at baseline and end of the study. 

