### Randomization

Study participants who meet the inclusion criteria will be enrolled. A random number generator website will be used to randomly assign patients to intervention or control groups: https://www.sealedenvelope.com/simplerandomiser/v1/lists. Patients will be randomized into intervention or control groups with a block size of four (1:1). At randomization, individuals will be stratified by GCS (3 to 8 and 9 to 13) and age (18 to 50 and 51 to 80) so that these variables will be equally distributed between the two groups. The sequence of allocation will be determined by permuted blocks of four. A block size of four creates six different blocks for assigning patients to the trial groups. There will be identical packets and labels for intervention and placebo, each with its own sequence number. One of the investigators who is not involved in patient care will generate the allocation sequence number.

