### Statistical methods

SPSS version 22 (SPSS Inc., Chicago, IL, USA) will be used to perform the analysis. For quantitative data, mean and standard deviation (SD) will be reported, and for qualitative data, frequency and percent will be reported. Kolmogorov-Smirnov test will be used to determine whether variables had a normal distribution (Ahad et al. 2011). Paired t-test will be applied to evaluate the differences in each group before and after the intervention. Independent t-test will be used to show the baseline and endpoint differences between the two groups. The Kruskal Wallis test will be used for the between-groups comparison, and the Wilcoxon Ranked Sum test for the inter-group comparisons, if the distribution of data is not normal. We will apply analysis of covariance (ANCOVA) to show differences between two treatment groups after adjusting for confounding variables. For missing data, an intention-to-treat analysis will be performed (Herman et al. 2009). Statistical significance is defined as a p-value less than 0.05.

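### Eleven biomarkers are all primary at p<0.05 while the trial is sized on CRP alone, so the chance of a false positive primary result is up to about 43%

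*Protocol article*

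**What the plan says.** In the protocol article, Outcome assessment opens with "Our primary outcomes will be serum levels of CRP, TNF-α, IL-6, IL-18, and ESR as a marker of inflammation" and continues with "serum LDH as an indicator of cell damage, TAC, SOD, GPx, MDA and catalase as an indicator of oxidative stress". All are to be measured at the start and end of the study. The next sentence lists the secondary outcomes separately (28-day mortality, GCS, CBC and the three clinical scores), so the primary label looks deliberate.

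Power calculation and sample size estimates rests on one of these markers: "CRP level was considered a main outcome". It uses 5% type I error, 80% power and Δ = 3 to reach 35 per group, then raises this: "Considering attrition, 90 patients will be considered in total, 45 in each group".

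Statistical methods sets one criterion: "Statistical significance is defined as a p-value less than 0.05". The article states no order of testing, no multiplicity adjustment, no requirement that several markers succeed together, and no special status for CRP in the analysis.

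**The concern.** Two sections disagree about what the trial is designed to test. The sample size section treats it as a trial of CRP. The outcome section treats it as a trial of eleven markers of equal standing.

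A 5% error rate holds for each marker taken alone, but it does not hold for the statement that saffron improved a primary outcome. The 80% power was derived for CRP; for the other ten markers the article gives no power at all.

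The headline conclusion is at stake. With eleven primaries and no success rule, one chance result could be presented as a positive trial of saffron in sepsis. The Discussion says that a favourable result could influence medical policy on saffron as an auxiliary sepsis treatment, so the trial cannot be excused as merely exploratory.

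**Working it through.** **Inputs**

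- Primary outcomes (Outcome assessment): CRP, TNF-α, IL-6, IL-18, ESR (5); LDH (1); TAC, SOD, GPx, MDA, catalase (5). Total 5 + 1 + 5 = 11.
- Threshold (Statistical methods): 0.05.
- Design (sample size section): type I error 5%, power 80%, Δ = 3, 35 per group before attrition, 45 per group enrolled. Allocation is 1:1 (Randomization).
- Not stated: the SD, the units of Δ, one- or two-sided testing, and the correlation between markers. Two-sided testing is assumed below unless noted.

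**The plan's own figure**

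The 35 per group can be neither confirmed nor refuted, because no SD is given. Using n = 2(1.96 + 0.84)² × SD² / Δ² with Δ = 3:

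- n = 35 needs an SD of about 4.48, a standardised effect of 3/4.48 = 0.67.
- SDs of 4, 5 and 6 would give 28, 44 and 63 per group.

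With the t-distribution in place of the normal approximation, the implied standardised effect is 0.679. The error rates below do not depend on any of this.

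**Familywise error**

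This is the chance of at least one p<0.05 when saffron affects none of the eleven markers, with one test per marker.

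- Independent tests: 1 − 0.95^11 = 1 − 0.569 = 0.431.
- Equally correlated two-sided normal tests, simulated with 400,000 draws:

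| Common correlation | Familywise error |
|---|---|
| 0 | 43% |
| 0.3 | 37% |
| 0.5 | 30% |
| 0.7 | 22% |
| 0.9 | 13% |

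For jointly normal two-sided test statistics, the Šidák inequality makes the independent case the maximum, so 43% is an upper limit under that model. Even at a correlation of 0.9 the error is more than twice 5%.

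**Would a correction across all eleven work at the planned size?**

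Bonferroni gives 0.05/11 = 0.0045 per test. The 80% below is an input, because the standardised effect of 0.679 was solved from 35 per arm and 80% power.

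| Analysed per arm | CRP power at 0.05 | CRP power at 0.0045 |
|---|---|---|
| 35 | 80% | 47% |
| 45 | 89% | 62% |

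The normal approximation gives 49% and 63% in the last column. About 61 per arm would be needed to restore 80%. If the sponsor's formula was one-sided, the implied effect is about 0.60, and two-sided Bonferroni power at 35 per arm is about 34%.

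**The case against.** The strongest reply is that this is a condensed article and that multiplicity is often left to a statistical analysis plan, which is not shown. The 0.05 criterion does not say that p-values are unadjusted, and an adjusted p-value could be read against it. That is fair as far as it goes: the absence of an adjustment is absence from this article only. But the choice of primary outcomes belongs in the protocol, and the article states that choice in full. A later adjustment would not make the outcome list agree with the sample size, and a Bonferroni correction over all eleven would cost most of the margin for CRP.

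A second reply is that 43% is the extreme case. It needs independent tests, all eleven nulls true, and a rule that any one marker suffices. The markers are related, so the true figure is probably lower; the range from 22% to 43% is the better summary. The any-one rule is not written down, but neither is any other.

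Third, the fall in power to 47% rests on a back-solved effect, two-sided testing, the post-attrition number and a conservative correction, and ignores any gain from the planned ANCOVA. Those caveats stand. With all 45 per arm analysed it is 62%, still short of 80%.

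Finally, a fixed testing order starting with CRP would also control the error. That is true, so a single primary is one sound remedy among others.

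**Conclusion.** The concern holds. The article names eleven unranked primary outcomes, sizes the trial on one of them, and gives a single 0.05 criterion with no rule for success. Followed as written, the chance of at least one false positive primary result is up to about 43%, or roughly 22% to 37% at common correlations of 0.7 down to 0.3. These figures assume no effect on any marker, one test per marker, and that any one significant marker counts. The correlations are assumptions.

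The stated 80% power applies to CRP alone, and only at an unadjusted 0.05. This must be fixed, because it decides what may be claimed as the trial's main result.

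**What to change.** Name CRP at the end of treatment (day 7 in Table 1) as the single primary outcome, tested two-sided at 0.05. Move TNF-α, IL-6, IL-18, ESR, LDH, TAC, SOD, GPx, MDA and catalase to secondary. Report them with confidence intervals, and either adjust them by Holm's method or label them exploratory. Make the Outcome assessment and sample size sections agree, and bring the analysis plan and the registry entry into line where they differ.

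The cost is wording: no patients, samples or assays are added, and the sponsor gives up calling ten markers primary. Because the article reports ethics approval of the whole protocol and patient selection from May 2024, the change may need an ethics amendment. If enrolment has begun, it should be dated, justified and made while treatment allocation is still blinded.
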